### Outcomes

The primary objective of this study is to investigate the feasibility and safety of a personalized pain psychotherapy approach with three different treatment modules. Based on the success of recruitment, randomization, assessment of outcomes, treatment adherence, treatment satisfaction, compliance and acceptability, clinical feasibility will be judged as ‘feasibility given’, ‘readjustment’ for the main trial necessary or ‘feasibility not given’.

Feasibility and safety outcomes will be documented and reported comparatively*Recruitment*: number of participants recruited over the study periodi.Successful recruitment of at least 105 participants (feasibility given)ii.Recruitment of 105 participants after modification of recruitment strategy (readjustment necessary)iii.Less than 105 participants after modification of recruitment strategy (feasibility not given)*Assessment of inclusion criteria*: proportion of potential participants assessed after written consent obtainedi.95% of potential participants completed after giving written consent (feasibility given)ii.75% of potential participants completed after giving written consent (readjustment necessary)iii.Less than 75% of participants completed after giving written consent (feasibility not given)*Randomization*: number of participants successfully randomized after completion of eligibility screening and baseline assessmentsi.Successful randomization of at least 105 participants after completion of eligibility screening and baseline assessments (feasibility given)ii.Randomization of 90 participants (15% dropout rate) (readjustment necessary dependent of retention rate)iii.Randomization of less than 90 participants (feasibility not given)*Retention* and *adherence*i.85% retention rate of 105 randomized participants, for end-of-treatment assessment at least at one of the end-of-treatment assessments (T_1_/T_2_) (feasibility given)ii.Retention of less than 85% of randomized participants, but reasons for dropout can be prevented by modification of study design (readjustment necessary)iii.Retention rate of less than 85% of those dropouts that are preventable by modification of study design (feasibility not given)*Treatment satisfaction, compliance and acceptability*i.Negative treatment effects: Unwanted and negative effects of the treatment will be assessed via the Negative Effects Questionnaire (NEQ) [41] supplemented by the subscales for negative effects on working place, partnership and family/peers of the Inventory for Assessing Negative Effects of Psychotherapy (INEP) [42].ii.Severe adverse events (SAEs) will be documented and reported descriptively.iii.Dropouts will be analysed according to the underlying reason for dropout and distinction will be made between those dropouts that are preventable by modification of study design and those that are not preventable by study design adjustment.

A secondary objective is the initial estimation of the efficacy and utility of such a personalized approach compared to a non-personalized approach on the different outcomes of the will outcome domains (pain intensity and physical functioning, emotional functioning and stress experience, participant ratings of improvement and satisfaction). Therefore, the exploratory analysis of the data will select the following candidate endpoints:Pain severity: Pain severity will be assessed via the pain severity subscale of the Multidimensional Pain Inventory (MPI-D) [27]. This subscale summarizes the items pain now, pain in the last week and suffering related to pain. The MPI-D is a valid instrument with a high reliability (Cronbach’s α ≥ 0.90).Disability/quality of life will be assessed via the Short-Form-Health Survey 12 (SF-12) and the Oswestry Disability Index (ODI). The SF-12 measures the impact of physical and mental health status on everyday life during the last 4 weeks. With the SF-12 the mental as well as the physical component can be assessed. It has a high validity and a good reliability for both, the mental and the physical component, with Cronbach’s *α* ≥ 0.75 and *α* ≥ 0.82, respectively [43]. The ODI captures the level of disability at the moment caused by pain in various activities of daily living (e.g. lifting weights, ability to care for oneself, ability to walk, ability to sit, sexual function, ability to stand, social life, quality of sleep and ability to travel). It is a validated questionnaire with good internal consistency [44].Anxiety and depression: the level of anxiety and depression of the last week will be assessed via the Hospital Anxiety and Depression Scale (HADS). With 14 items, the HADS is a self-assessment scale that measures anxiety and depression through two subscales. Seven items for each subscale are rated by the patients on a 4-stage response format. It was in particular developed for somatic disorders and physical symptoms were therefore excluded. The HADS has high validity and reliability [45].Positive and negative affect: Affectivity will be assessed via the Positive and Negative Affect Schedule (PANAS). This scale captures both positive and negative affectivity by asking for an assessment of positive and negative states of mind during the last week on a 5-point scale ranging from “not at all” to “extremely”, assessed on 20 items. It has a good validity and reliability with Cronbach’s α ≥ 0.86 [46, 47].Global impression of change: Global impression of change will be assessed from both the patient’s (patient’s global impression of change, PGIC) and the therapist’s perspective (therapist’s global impression of change, TGIC). It is a 7-point scale with answers coded from “very much improved” to “very much worse”.Days out of work (socioeconomic aspect) and change in medication since start of treatment will be assessed via additional items.Activity levels will be assessed based on EMA sampling, with 10 queries per day, assessing for example pain intensity, attention to pain, pain catastrophizing, fear of pain and positive/negative affect.

For endpoints 1–6, the change between T_0_ and T_1_ (or 3-month follow-up) will be used as the outcome variable. In addition, the candidate endpoint domains will be investigated after 4 and 8 weeks to explore temporal therapy effects and dose-response relationships.

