### Sample size calculation

The study will be performed in an exploratory fashion and is planned as a pilot study to describe the feasibility and safety of personalized treatments for CMSP as a primary outcome, as well as an initial estimation of signals efficacy and utility as secondary outcomes. Even though a formal power calculation is not necessary in a pilot study, we nevertheless performed a power calculation to better estimate the initial signals of efficacy and utility.

For power considerations, we use a mixed-model with repeated measurements (MMRM), a two-sided significance level of 5% and a sample size of 90 patients (→45 per study arm →90 total from a total of 105 patients at an assumed dropout rate of 15%). The MMRM takes into account also the interim measurements for each patient and allows therefore a fuller use of the data than an ANCOVA. The sample size of 105 patients allows to calculate our feasibility measures with a 95% confidence interval width from 11 to 19% (for varying proportion 0.1–0.5) based on a Wald interval for binary measures [40]. Moreover, patients with data with at least one measurement can be used for the primary analysis; therefore, we expect fewer patients not to be usable for the analysis compared to an ANCOVA. Between repeated measurements, a correlation of 0.3 is assumed. Then, the study has a power of 80% to detect a true effect size of *f* = 0.22, a power of 85% for *f* = 0.23 and 90% power for a true effect size of *f* = 0.25. Dropouts will be analysed according to the underlying reasons for dropout and distinction will be made between those dropouts that are preventable by modification of study design and those that are not preventable by study design adaptations.

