### Feasibility

Feasibility will be assessed according to the following criteria: recruitment, assessment of inclusion criteria, randomization, retention and adherence, treatment satisfaction, compliance and acceptability. On the basis of these criteria, we will assess whether (1) feasibility is completely given, (2) feasibility is limited but likely to be achieved with adjustment of the study procedure or (3) feasibility is not given.

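### Retention rule (iii) is misstated: it attaches the lowest feasibility verdict to preventable dropout, cannot be computed, and leaves non-preventable dropout without a verdict

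*Protocol article*

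**What the plan says.** All references are to the protocol article.

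Feasibility and safety are the primary objective. Under Outcomes, "clinical feasibility will be judged as ‘feasibility given’, ‘readjustment’ for the main trial necessary or ‘feasibility not given". Retention and adherence is one of the criteria, with three steps:

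- (i) Feasibility given: "85% retention rate of 105 randomized participants, for end-of-treatment assessment at least at one of the end-of-treatment assessments" (T1 or T2).
- (ii) Readjustment: "Retention of less than 85% of randomized participants, but reasons for dropout can be prevented by modification of study design (readjustment necessary").
- (iii) Not given: "Retention rate of less than 85% of those dropouts that are preventable by modification of study design (feasibility not given").

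Three other statements bear on how these should be read:

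- Sample size calculation says that dropouts will be analysed by reason and that "distinction will be made between those dropouts that are preventable by modification of study design and those that are not preventable by study design adaptations". The last item of the feasibility list in Outcomes repeats this.
- Feasibility describes the middle and lowest verdicts as "feasibility is limited but likely to be achieved with adjustment of the study procedure or (3) feasibility is not given".
- Sample size calculation plans for "90 total from a total of 105 patients at an assumed dropout rate of 15"%, which is where the 85% comes from.

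**The concern.** Step (iii) has three faults.

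1. **It cannot be computed.** It takes a retention rate among dropouts, who by definition were not retained.
2. **It names the wrong class.** Preventable dropout is already the condition for readjustment in step (ii). Step (iii) gives the same class the worst verdict.
3. **It leaves a gap.** The protocol separates preventable from non-preventable dropout, but no retention step mentions the non-preventable class, for which a verdict of not feasible would be expected.

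Efficacy p-values in this pilot are to be read descriptively only, and the pilot is meant to prepare a multi-centre trial. The feasibility criteria therefore carry much of what it will report. If retention falls short, two readers applying the published rule in good faith could report different verdicts.

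**Working it through.** **Inputs.** Planned number randomized 105, evaluable 90, dropout 15% (Sample size calculation). Retention threshold 85% and the three steps (Outcomes). Meaning of the verdicts (Feasibility).

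**The plan's own figure.** 90 / (1 − 0.15) = 105.9, so 106 when rounded up, against 105 stated. The difference is one patient, and the 105 and 85% are not in question.

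**Where the threshold falls.** 0.85 × 105 = 89.25. So 90 retained (90/105 = 85.7%) meets step (i), and 89 (89/105 = 84.8%) does not. Steps (ii) and (iii) matter from 89 downwards.

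**How likely that is.** Exact binomial probability of 89 or fewer retained out of 105, for three assumed true retention rates:

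| True retention (assumed) | P(89 or fewer) |
|---|---|
| 80% | 91% |
| 85% (planned) | 51% |
| 88% | 19% |

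The threshold sits at the planning value, so the faulty part of the rule may well be needed.

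**Verdicts under two versions of step (iii).** Because the sentence is not computable, the middle column has to assume that it means retention of randomized patients below 85% with preventable dropout, which keeps the class it names.

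| Retained of 105 | Reason for dropout | Step (iii) keeping 'preventable' | Step (iii) with 'not preventable' |
|---|---|---|---|
| 90 | either | given | given |
| 89 or 80 | all preventable | readjustment and not given | readjustment |
| 89 or 80 | all non-preventable | none | not given |
| 89 or 80 | mixed | unclear | unclear |

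Inserting 'not' settles the pure cases. It does not settle mixed reasons.

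**Two charitable readings that avoid the contradiction.** Take 80 of 105 retained (76.2%), so 25 dropouts, of which 12 are preventable.

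- (a) Not feasible if fewer than 85% of the dropouts are preventable: 12/25 = 48%, so not given.
- (b) Not feasible if retention stays below 85% after adding back preventable dropouts: (80 + 12)/105 = 92/105 = 87.6%, so readjustment.

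Neither is what the sentence says, and they disagree on the same data.

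**Check against the Feasibility section.** It reserves the middle verdict for shortfalls that adjusting procedures could repair. Preventable dropout fits that description. Step (ii) agrees with it; step (iii) as printed does not.

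**The case against.** The strongest reply is that this is a slip of wording and that the intent can be recovered. Step (ii) is built as a contrast, the protocol twice separates the two classes of dropout, and the Feasibility section shows which verdict belongs to which. All of this points to a missing 'not'. That stands as the likeliest explanation. It does not make the printed rule usable, and the corrected word would still not say what to do with mixed reasons.

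A reader might infer something stronger: that every result below 85% returns two opposite verdicts or none. The document does not support that. The double verdict appears only if an uncomputable sentence is first replaced by one particular reading. Under reading (a) in the working, the same pure cases each get a single verdict. Readjustment and not given are also neighbouring levels, not opposites. What is established is ambiguity.

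A reader might also infer that the decision on the main trial would be made after the data are seen. That does not follow either. Retention is one of several criteria judged together, nothing makes it binding alone, and the article promises an analysis plan fixed before analysis, which is not shown here and may state the rule properly.

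Finally, it may be said that mixed reasons are operational detail that an article can leave out. Taken alone, that is fair. But the article does print the decision rule, and prints it wrongly, so this is more than an omission, and mixed reasons should be covered when the rule is corrected.

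**Conclusion.** The point holds as a misstated decision rule within the primary feasibility outcome. Step (iii) has no computable meaning, names the class already assigned to readjustment, conflicts with the Feasibility section, and leaves non-preventable dropout without a verdict. One of several feasibility criteria therefore cannot be applied unambiguously when retention is below 85%, that is, at 89 or fewer if 105 are randomized.

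The 51% chance of reaching that region assumes 105 randomized, independent dropout and a true retention of exactly 85%; the range shown is 19% to 91% for true retention of 88% down to 80%. The lost 'not' is inferred. The fault is in the wording of one criterion; the 85% threshold, the sample size and the three-level scheme are unaffected.

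**What to change.** Before outcome data are reviewed, restate step (iii) as retention below 85% of randomized participants where the dropout could not have been prevented by changing the design. Then word (i) to (iii) so that every result falls in exactly one of them, including mixed reasons. One workable form, as proportions of those actually randomized:

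- (i) given: retention at least 85%;
- (ii) readjustment: retention below 85%, with non-preventable dropouts at most 15%;
- (iii) not given: non-preventable dropouts above 15%.

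With 105 randomized, 0.15 × 105 = 15.75, so the line between (ii) and (iii) is 15 or fewer versus 16 or more non-preventable dropouts. These counts hold only for 105. The randomization criterion also provides for 90 randomized, where 0.15 × 90 = 13.5 gives 13 versus 14. Proportions are therefore safer than fixed counts.

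This form treats every preventable dropout as recoverable in the main trial, which is optimistic. The sponsor may prefer another split, provided it is fixed in advance. Dropouts with no known reason should also be assigned to a class, or the rule is still not exhaustive.

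The cost is the rewording of one criterion, carried into the analysis plan. No further data are needed, because reasons for dropout are already to be recorded and analysed.

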Feasibility objectives will be quantified. If appropriate, 95% confidence intervals will be calculated based on the Wilson Score interval for binary measures. We favoured the Wilson Score interval against Wald interval due to their good properties for small numbers of trials, compared to Wei and Hutson [40]. For the analysis of the primary outcome, we will use the complete and pseudonymized data set and follow the intention-to-treat approach which includes all patients in the group they were allocated to by randomization. This approach preserves the allocation of treatment by randomization and it will be as close as possible to the ITT ideal of including all randomized patients. As sensitivity analysis, the analysis will be repeated in the per-protocol (PP) set, excluding patients with major protocol violations. Additional sensitivity analyses will explore the effects of the treatments the patients actually received. The null-hypothesis H0 (no difference occurs in the population means with regard to pain severity at T1 between the experimental intervention and the control intervention) will be tested against H1 (there is a difference in the population means of pain severity differences between the two groups at T1 and T0). Provided that the model assumptions are fulfilled, the null hypothesis will be tested using a (robust) mixed linear regression model at a significance level of 5%. The primary outcome (pain severity at T1, difference to T0) will be analysed using mixed-effects model repeated measurements after 4, 8 and 12 weeks (=T1). The analysis will be adjusted for condition, gender and baseline (T0) pain severity. Compound symmetry will be assumed. Because of the exploratory nature of the study, the observed initial signals of efficacy and utility will be considered more important than the *p*-values. The corresponding *p*-values of these tests will be interpreted purely descriptively. We will compute effect sizes and interpret them together with the respective 95% confidence intervals. Regarding secondary endpoints, exploratory data analysis will be performed using appropriate analytical methods depending on the respective parameter. Details of the statistical analyses will be fixed in a statistical analysis plan developed by the statistics department of IZKS Mainz prior to database closure. The safety analysis includes calculation and comparison of frequencies and rates of adverse events. Furthermore, statistical methods are used to assess the quality of data and the homogeneity of intervention groups. All analyses will consider gender aspects. Prior to all analyses, we will pre-specify a statistical analysis plan.

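### The change-from-T0 rule for endpoints 1–6 cannot be applied to the global impression of change or medication-change items, and T0 adjustment should be stated for endpoints 2–4 as it is for pain severity

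*Protocol article*

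**What the plan says.** The Outcomes section lists seven candidate endpoints for the secondary objective. In the order given they are:

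1. pain severity (MPI-D subscale)
2. disability and quality of life (SF-12, ODI)
3. anxiety and depression (HADS)
4. positive and negative affect (PANAS)
5. global impression of change, rated by patient and therapist
6. days out of work and change in medication
7. activity levels from EMA sampling

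After the list comes the rule: "For endpoints 1–6, the change between T_0_ and T_1_ (or 3-month follow-up) will be used as the outcome variable". No exception is made.

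On endpoint 5 the article says: "It is a 7-point scale with answers coded from “very much improved” to “very much worse". On endpoint 6: "Days out of work (socioeconomic aspect) and change in medication since start of treatment will be assessed via additional items".

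The Statistical analyses section gives a model for pain severity only: the difference to T0, in a mixed model over weeks 4, 8 and 12, with the T0 pain score among the covariates. On the covariance it says "Compound symmetry will be assumed". For the other endpoints it leaves the method to suit each measure, with details to follow in a SAP. The Sample size calculation section says: "Between repeated measurements, a correlation of 0.3 is assumed".

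**The concern.** There are two separate issues.

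The first is definitional. A transition rating asks how things have changed since treatment started. Before treatment there is nothing to rate, so no T0 score exists and none can be subtracted. Applied as written, the rule gives no outcome variable for PGIC, TGIC or the medication-change item. PGIC matters because participant-rated improvement is one of the outcome domains the article names.

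The second is precision. A change score that is not also adjusted for its T0 value carries the baseline noise into the outcome. When T0 and T1 are only moderately correlated, its variance is clearly larger than that of a baseline-adjusted comparison. The article puts effect sizes and their 95% confidence intervals ahead of p-values, and the pilot is meant to prepare a multicentre trial, so the width of those intervals matters. T0 adjustment is written down for endpoint 1 and not for endpoints 2–4.

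**Working it through.** **Which endpoints the rule can reach**

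- Endpoints 1–4 are scores on a scale that can be completed at T0 and again at T1. A difference can be formed.
- Endpoint 5 runs from improved to worse. The score is itself the change, and no T0 score is possible.
- Endpoint 6, medication item, is defined as change since the start of treatment. Again no T0 score is possible.
- Endpoint 6, days out of work, can be differenced only if a comparable period before T0 is recorded. The article does not say whether it is.

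So the rule fails for one whole endpoint and half of another.

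**Where the correlation of 0.3 comes from**

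The stated power is 80%, 85% and 90% at f = 0.22, 0.23 and 0.25, with "a two-sided significance level of 5% and a sample size of 90 patients". A between-group repeated-measures F test has noncentrality f²·N·m / (1 + (m − 1)ρ), with 1 and N − 2 degrees of freedom. Take N = 90, ρ = 0.3 and m = 3. The value of m is inferred from weeks 4, 8 and 12; the sample size section does not give it.

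- f = 0.22: 0.0484 × 270 / 1.6 = 8.17, power 80.7%
- f = 0.23: 0.0529 × 270 / 1.6 = 8.93, power 84.0%
- f = 0.25: 0.0625 × 270 / 1.6 = 10.55, power 89.5%

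The stated figures are reproduced to within about one percentage point. The 0.3 therefore belongs to the repeated measurements in this power model. The article does not give it as the T0–T1 correlation of the SF-12, ODI, HADS or PANAS. Using it there is an assumption, so a range is shown.

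**Change scores with and without the T0 covariate**

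Assume one post-treatment time point, equal variance σ² at T0 and T1, and correlation r.

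- Unadjusted change: variance 2(1 − r)σ²
- Adjusted for T0: variance (1 − r²)σ²
- Ratio: 2(1 − r) / (1 − r²) = 2 / (1 + r)
- Ratio of confidence interval widths: the square root of that

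| r | Unadjusted change (σ²) | Adjusted (σ²) | Variance ratio | Interval width |
|---|---|---|---|---|
| 0.3 | 1.40 | 0.91 | 1.54 | about 24% wider |
| 0.5 | 1.00 | 0.75 | 1.33 | about 15% wider |
| 0.7 | 0.60 | 0.51 | 1.18 | about 8% wider |

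A simulation of 4,000 trials with 45 patients per arm and r = 0.3 gave a variance ratio of 1.52.

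**Why pain severity is not affected**

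If change is regressed on treatment and T0, then Y1 − Y0 = a + b·treatment + c·Y0, which is the same as Y1 = a + b·treatment + (c + 1)·Y0. The treatment coefficient b is identical in both forms. In the simulation the largest difference between the two estimates was 2 × 10⁻¹⁵, which is rounding error. Because T0 pain severity is a stated covariate, using change as the outcome costs nothing there.

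**The case against.** The strongest reply has three parts.

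*The transition items measure change directly, so the rating itself satisfies the rule.* This is the sensible intention, and it is why the defect is easy to repair. It does not make the sentence correct. One statement would have to mean a computed difference for endpoints 1–4 and a raw rating for endpoint 5 and part of endpoint 6. Leaving the method to suit each measure chooses an analysis; it does not redefine the outcome variable. A reader might infer that participant-rated improvement has no valid analysis at all. That goes too far: the rating can be analysed as it stands, and the flexibility over methods leaves room for an ordinal model.

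*Silence on T0 adjustment for endpoints 2–4 is not a decision against it.* This stands. The article names the outcome variable for these scales but fixes no model, and the one model it does give combines change with T0 adjustment. It would be wrong to say that these effects will be estimated inefficiently. The precision loss follows only if the covariate is left out.

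*The 0.3 is borrowed from the power model.* This also stands, and is why the range from 0.3 to 0.7 is given. A reader might go on to compute the power lost on the secondary endpoints. The documents do not support that: the stated effect sizes belong to the repeated-measures calculation, and p-values are to be read descriptively only.

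**Conclusion.** The definitional point holds without any numerical assumption. The rule covers endpoints 1–6 with no exception, and PGIC, TGIC and the medication-change item have no T0 value from which to form a change.

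The precision point holds only as a conditional. If endpoints 2–4 were analysed as change without their T0 covariate, the variance would be 1.54, 1.33 or 1.18 times the adjusted variance at r = 0.3, 0.5 or 0.7. This rests on equal variances at T0 and T1, a single post-treatment time point, and an assumed correlation for these scales.

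It is tempting to say that change from T0 is inefficient for every remaining endpoint at the plan's own correlation. The documents do not support that. Pain severity is already adjusted for T0 and loses nothing; for the others the model is not fixed and the correlation is not given. Nor do they show that a T0 value for days out of work will be collected.

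These are exploratory secondary endpoints in a feasibility pilot, so the consequence is an unworkable definition and possible imprecision, not a false confirmatory claim. The correction is specific and nearly free, so it should be made.

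**What to change.** In the SAP, before database closure:

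- Limit the change rule to endpoints 1–4. Include days out of work only if a comparable T0 period is recorded, and say which period that is.
- Define the outcome for PGIC, TGIC and medication change as the rating at T1 (and at T2 where collected), with no baseline subtraction, and analyse it with an ordinal or categorical method.
- State that the SF-12, ODI, HADS and PANAS analyses each include the scale's own T0 value as a covariate, as the pain severity model already does.

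The cost is a few sentences. No new data are needed for endpoints 2–4, because the change rule already presupposes their T0 scores, and none for the transition items, because the rating itself becomes the outcome.
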